##### SN Data Statistical Power

We powered the matched cluster evaluation trial to have .80 power to detect a reduction in 12-month incident SV (the primary outcome) at α<.05. We estimated we would have a follow-up sample of 791 youth study participants (baseline sample: n=953, 791/953, estimated 85% retention at follow-up) from the SN data collection across 22 study sites (11 C2H and 11 control; estimated 36 youth per cluster). We assumed that the average baseline 12-month incidence of the primary outcome would remain constant for the control group at follow-up (107/395, 27% past 12 months SV). The minimal detectable effect would therefore be a 32% (.27 × .32) reduction in SV (71/396, 18% for 12 months incidence at follow-up). Reducing SV by 32% is feasible, given that a previous rigorous evaluation of the shifting boundaries SV prevention model detected a 43% and 50% reduction in SV [40,41]. Furthermore, 37.5% (297/791) of the sample identified as a sexual and/or gender minority (ie, LGBTQ+), among whom 42.4% (126/297) report SV. Estimating the minimal detectable effect for this subsample (297/791 of follow-up participants, 37.5%, 14 LGBTQ+ youth per site), and a 42.5% baseline incidence for LGBTQ+ controls, this study was also powered to detect a 33.5% (0.335 × 0.425=0.14; 0.425-0.14=28% for 12 months incidence at follow-up, 83/297) reduction in LGBTQ+ SV experiences.

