Our primary analysis for main effects (aim 2) will be designed to assess the effects of the intervention on the prevalence of past 12-month SV and DV (sexual assault, online and in-person SH, DV, and LGBTQ+-specific SV) at 24-month follow-up. Our secondary analysis for secondary outcomes (aim 2) will be designed to assess the effect of the intervention on SV attitudes, behavioral intentions to intervene to prevent SV, reported intervention behavior, perceived behavioral self-efficacy to prevent SV, social norms of the acceptability of SV, and community connection and cohesion. First, we will conduct descriptive analyses to explore differences at baseline between the intervention and control groups and factors associated with loss-to-follow-up to understand how these factors may contribute to possible bias in our results. Then, we will assess change over time and by group via adjusted hierarchical difference-in-differences regression analyses to account for unmeasured and measured baseline differences between intervention and control groups, controlling for sampling level (ego, alter 1, and alter 2), accounting for clustering by community, and confounders identified using a dialectical acyclic graph [54]. The difference-in-differences approach does not rely on the strength of the match between intervention and control groups, but rather accounts for baseline differences, offsetting the impact of the three poor intervention-control matches that exist in the sample. Furthermore, we will adjust for factors associated with treatment group assignment to further account for baseline differences. In sensitivity analyses, we will use modern difference-in-differences approaches, such as group weighting approaches proposed by Callaway and Sant’Anna [55], to account for recent developments in understanding potential violations of parallel trends. Subanalyses will be conducted to assess for interaction at each sampling level (ego, alter 1, and alter 2), by gender, LGBTQ+ identity, race or ethnicity, and triangulating with process data. Process data effect modification analyses will assess whether implementation quality, program dosage, and characteristics of program sites modify the observed effect of the intervention on primary and secondary outcomes. Sensitivity analyses will be conducted to assess the variability of effects related to potential violations of the parallel trend assumption, low response rates if they unexpectedly occur, and bias due to potential differences in intervention and control response rates. In addition to the intention-to-treat analysis described above, we will conduct an as-treated analysis based on individual-level dosage estimates from process data. Finally, we will conduct a sensitivity analysis to account for loss-to-follow-up using inverse probability of censoring weighting [56] based on baseline data, should significant baseline differences exist between those lost and those retained. All analyses will be complete case analyses.

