## Results

This study was funded in September 2020 for three years and was given two additional years of funding through a competitive renewal (through September 2025). A no-cost extension was granted through September 2026. Institutional review board approval was granted in February 2021. Baseline survey data were collected on a rolling basis between October 2021 and June 2023 from 953 participants of the SN sample. Baseline data were analyzed in 2025, and results related to the SN structure are expected to be published in the fall of 2026. Follow-up survey data were collected from September 2023 to November 2025 from 746 participants. Main effect analysis will take place from summer to fall 2026. Main effect findings will be published in late 2026 or early 2027.

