### Strengths and Limitations

There are a variety of limitations to this study that should be considered with regard to interpreting results. First, random assignment of the intervention was not possible, given preselection by a funder of the intervention sites. Exchangeability between intervention and control groups was strengthened by propensity score matching of control communities and strategic selection of a comparable control program from which to recruit control participants, yet for three control sites, the quality of control group matching was limited. We will use multiple strategies to try to address limits to exchangeability in our results, including the use of a quasi-experimental analytical approach (difference-in-differences) that accounts for baseline differences and covariate adjustment to control for baseline differences between the intervention and control groups. Second, there are multiple ways in which selection bias may affect our results. For example, participants were not randomly selected and instead were eligible to be in the sample based on their choice to sign up for the program (C2H or 4-H). The types of youth who may volunteer to join such a group are likely systematically different from the youth population in California, limiting the generalizability of the findings. While findings may not be generalizable to the state, because this study is being conducted across 22 communities across all regions of the state, it does include a diverse sample of youth and communities, and likely will provide relevant findings for other diverse communities that might consider implementing C2H in the United States. Third, we may observe nonrandom loss to follow-up at the 24-month follow-up. While we have used extensive efforts to keep the sample of youth engaged and retained over this long follow-up period, we will also likely need to reduce the impact of this form of selection bias by using inverse probability of censoring weighting in our analyses. Finally, this study began during the COVID-19 pandemic, with baseline data collection and intervention initiation occurring between 2021 and 2023. While we expect the pandemic to have impacted control and intervention communities in similar ways, our ability to observe diffusion of intervention effects across SNs may be limited due to the way the pandemic may have caused disruptions to the stability of youth’s SNs between baseline and follow-up. Furthermore, implementation of the C2H model was likely disrupted by the “Great Resignation” that occurred between 2021 and 2022 in the aftermath of the COVID-19 pandemic, in which an unprecedented number of US workers quit their jobs, including prevention staff at C2H implementing organizations [59]. We would expect that the Great Resignation would have a greater impact on C2H implementation than 4-H implementation because adults facilitating C2H groups were primarily paid staff, and 4-H facilitators were more often long-term volunteers who often had children in the program. Despite these limitations in this study’s design and external factors that may have impacted implementation of the C2H program, this study uses a rigorous quasi-experimental design complemented with quasi-experimental analytic techniques to account for the real-world, practical challenges of evaluating community-level programs. Moreover, this study is strengthened by its SN sampling design and implementation in 22 diverse communities.

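### Weighting for the 21.7% lost to follow-up depends on finding significant baseline differences, and even then leaves the primary complete-case estimate uncorrected

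*Protocol article*

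**What the plan says.** Under Analysis of SN Data, the main analysis is an adjusted hierarchical difference-in-differences regression. Censoring weights based on baseline data come last in the list, as a sensitivity analysis. The condition for running them, and the rule that follows, read: "should significant baseline differences exist between those lost and those retained. All analyses will be complete case analyses". The same section refers to the main model with "In addition to the intention-to-treat analysis described above", as a contrast to an as-treated analysis based on dosage.

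The section also plans two things that do not depend on this condition: a descriptive first step on factors associated with loss, and sensitivity analyses for low response and for response that differs between intervention and control. No method is named for the latter.

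Strengths and Limitations expects that loss may be non-random and is firmer about the remedy: "we will also likely need to reduce the impact of this form of selection bias by using inverse probability of censoring weighting".

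The amount of loss is already known. Results states "Baseline survey data were collected on a rolling basis between October 2021 and June 2023 from 953 participants of the SN sample" and "Follow-up survey data were collected from September 2023 to November 2025 from 746 participants". SN Data Statistical Power had planned on "baseline sample: n=953, 791/953, estimated 85% retention at follow-up".

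**The concern.** Three features of the rule work together.

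- **The trigger.** Whether loss is handled at all depends on finding a significant difference. With 207 lost youth, a moderate difference can easily be missed, and absence of significance is not evidence that the completers represent everyone enrolled.
- **The target.** The comparison is worded as lost versus retained, with no mention of arm. A DiD on completers is distorted when outcome-related loss differs between arms. Gaps that run in opposite directions in the two arms can cancel in a pooled comparison.
- **The status.** Even when the condition is met, weighting is a sensitivity analysis. The headline estimate remains the unweighted complete-case DiD whatever the check shows.

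At stake is the main effect on past 12-month SV and dating violence (DV), estimated on 78.3% of those enrolled. The authors themselves expect that a correction will probably be needed.

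**Working it through.** **1. Loss.** 953 − 746 = 207, and 207/953 = 21.7%. Planned: 791/953 = 83.0% retained, so 17.0% lost. (The printed 85% would give 0.85 × 953 = 810.)

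**2. The plan's own benchmark.** The power section aims "to have .80 power to detect a reduction in 12-month incident SV (the primary outcome) at α<.05", with a control rate of "107/395, 27% past 12 months SV" and a 32% relative reduction. So Δ = 0.27 × 0.32 = 0.0864 (8.6 points) and the target rate is 0.1836.
- Two-proportion formula, two-sided 0.05 (sidedness is not stated): n = [1.96·√(2 × 0.2268 × 0.7732) + 0.842·√(0.27 × 0.73 + 0.1836 × 0.8164)]² / 0.0864² = 368 per arm.
- With continuity correction this is 391 per arm, 782 in total, against 791 stated. The figure reproduces to about 1%, with no visible allowance for clustering.
- At 746 (373 per arm assumed), power without clustering is 80.6%. The issue is therefore mainly bias, not lost sample size.

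**3. Power of the trigger.** Assumptions: overall baseline SV 27%, independence, one pooled two-sided test at 0.05, 207 lost against 746 retained.
- Null SE = √[0.27 × 0.73 × (1/746 + 1/207)] = 0.0349.
- For a gap d, retained rate = 0.27 − d × 207/953, and lost rate = retained rate + d.

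| Gap in baseline SV | Retained | Lost | Power |
|---|---|---|---|
| 5 points | 25.9% | 30.9% | 30% |
| 7 points | 25.5% | 32.5% | 52% |
| 10 points | 24.8% | 34.8% | 81% |

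Under an assumed design effect of 1.35 these fall to 24%, 41% and 69%.

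Testing by arm would not rescue the approach. For a difference between arms in the lost–retained gap, SE = √[0.27 × 0.73 × (2/373 + 2/103.5)] = 0.0698, so power for a 10-point difference is about 30%.

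**4. Effect on the DiD, by assumed scenario.** Assume no true effect, 27% baseline SV in both arms, follow-up SV risk of 50% with baseline SV and 18.6% without, control loss unrelated to SV, equal arms, 78.3% control retention and no covariate adjustment. In the full population, follow-up SV = 0.27 × 0.50 + 0.73 × 0.186 = 27.08%, a change of +0.08 points.

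*Scenario A: C2H retention 70% with baseline SV, 81% without.*
- Retained fraction: 0.27 × 0.70 + 0.73 × 0.81 = 0.7803.
- Completers' baseline SV: 0.189/0.7803 = 24.22%.
- Completers' follow-up SV: 0.2422 × 0.50 + 0.7578 × 0.186 = 26.21%.
- DiD = (26.21 − 24.22) − 0.08 = **+1.9 points**, 22% of 8.64.
- Pooled baseline SV is 31.96% in the lost and 25.61% in the retained, a gap of 6.35 points. The trigger fires about 45% of the time.

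*Scenario B: C2H retention 60% and 85%.*
- Retained fraction: 0.162 + 0.6205 = 0.7825.
- Completers' baseline SV: 0.162/0.7825 = 20.70%. Follow-up SV: 25.10%.
- DiD = (25.10 − 20.70) − 0.08 = **+4.3 points**, half of 8.64.
- Pooled baseline SV is 38.34% in the lost and 23.85% in the retained, a gap of 14.5 points. The trigger fires about 98% of the time.

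Scenario A shows the weakness of the trigger. Scenario B shows the other one: the trigger almost always fires, yet the primary estimate stays at +4.3.

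**The case against.** Much can be said for the plan, and part of it stands.

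- **Weighting as a sensitivity analysis is a legitimate choice.** It corrects only loss explained by measured baseline variables. This stands, so making the weighted analysis primary is a preference; running it unconditionally is the necessary part.
- **The trigger may be wider than modelled.** No test, threshold, variable list or pooling rule is given. A trigger covering several baseline factors would open more often than the figures above. This is fair. But if no formal test is meant, the condition is undefined and leaves the decision to discretion after the data are seen.
- **Differential response is not ignored.** The separate sensitivity analyses address it. They name no method, however, and do not alter the primary estimate.
- **The intention-to-treat label.** A reader might call it wrong for a completer analysis. The section uses it only as the opposite of as-treated, so it is defensible for group assignment. What it leaves unclear is that the lost youth are excluded.
- **The two sections on weighting.** A reader might infer a contradiction. They differ in firmness: a likely need is compatible with a conditional plan, and a sensitivity analysis is still one of the analyses.
- **Staff turnover as a cause of arm-specific loss.** A reader might infer this from the remarks on resignations under Strengths and Limitations. Those remarks concern C2H implementation. Under Recontacting and Retention and Follow-Up SN Data Collection, research staff made the check-ins, and the 24-month survey was completed through an online link. The documents do not support that mechanism.

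**Conclusion.** The point holds as a should-fix. The article fixes a rule under which handling of 21.7% loss depends on a significant difference, and under which the primary estimate is never corrected for loss. The trigger would miss a 5-point gap in baseline SV about 70% of the time and a 7-point gap about half the time, given 27% baseline SV, independence and one pooled two-sided test.

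A reader might go further and infer that the primary result will be biased, or biased in favour of C2H. The documents do not support that. Loss by arm is not reported, so neither size nor direction can be computed. The +1.9 and +4.3 points rest wholly on assumed retention and repeat-risk figures, and in both cases C2H looks worse than it is, so a real benefit would be masked. Nor is it right that the bias matters only when the trigger stays shut: in the larger scenario it opens about 98% of the time and the headline estimate is still unweighted.

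**What to change.** Before outcome analysis, scheduled for summer to fall 2026:

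1. Delete the significance condition on the weighting.
2. Prespecify one analysis that accounts for loss, always run and reported beside the complete-case DiD, preferably as primary. Either use arm-specific censoring weights built from baseline SV and DV, age, LGBTQ+ identity and sampling level, or a likelihood-based hierarchical model that keeps all 953 baseline records. The second option also means amending the rule that every analysis is complete-case.
3. Make Analysis of SN Data and Strengths and Limitations say the same thing about whether weighting will be used and in which analysis.
4. Describe the unweighted model as complete-case by assigned group.

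The cost is wording, modest programming on baseline data already in hand, and slightly wider intervals. The report should say that weighting removes only bias from loss explained by the measured baseline variables.

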Once a nominated peer accessed the survey link (on their own device, in a location or time of their choice), they completed the same assent or consent form as egos, followed by a modified eligibility screening that included confirmation of being between the ages of 14 and 24 years, being new to the survey (ie, not having taken it before), and knowing the person that nominated them. Additionally, when a nominated peer accessed the survey link, a US $10 incentive was sent to their ego nominator in acknowledgment of their time and effort to recruit their peer. Once screened, these peers became “alter 1s,” received the same survey, the same opportunity to nominate up to 10 peers (yielding potential “alter 2s”), and the same request for providing their contact information and their nominated peer’s contact information as the egos. Upon completion of a survey by an alter 1, the alter 1 received a US $20 gift card within 24 hours. Alter 2 recruitment and participation mirrored that of alter 1 s except they were not asked to nominate peers or provide peer contact information. Alter 2 s received a US $25 gift card for taking the survey, and alter 1, who nominated them, received US $10 when they accessed the survey link. Alter 1 and alter 2 surveys included an embedded video created by the YRAB explaining this study and the risks and benefits of participation, providing similar information as is provided during the ego survey orientation.

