### Data Analysis

#### Analysis of SN Data

The primary outcomes, SV and DV, were analyzed as binary variables, constructed as lifetime and past 12-month indicators of experiencing that form of violence. Secondary outcomes, most of which are assessed as scales, were continuous variables based on mean scores across included items.

We used baseline SN data to understand the clustering of social norms and behaviors within this study’s population (aim 1). To do this, we have described the network characteristics of the sample and assessed how SV social norms and experiences of SV and DV are associated among nominator-nominee dyads. We used dyadic observations from the baseline data for each pair of socially connected youth (dyad; eg, ego and alter 1, and alter 1 and alter 2) to restructure the dataset. We calculated whether having a peer who adheres to a particular norm or behavior was predictive of corresponding responses from paired versus nonpaired individuals. This was done using logistic regression analysis (outcome: yes or no) using a generalized estimating equation to account for correlation among dyads. We assessed for effect modification of these relationships based on the types of relationships (eg, school or other peer, or family), the mode of communication, gender concordance, and racial concordance. This analysis provided us with pertinent insight into what norms, attitudes, and behaviors were clustered among socially connected people, and across what relationships, creating a map for understanding opportunities for SN-based intervention. This manuscript is in preparation for publication.

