
Additionally, using SN data, we will test for social diffusion of intervention via SNs (aim 2) via multiple methods. To test the effect of social influence on attitudes, norms, and behaviors, we will use the dyadic dataset of nominator-nominee pairs to test for the effect of social contacts’ attitudes, norms, or behaviors at 24-month follow-up, controlling for both of their own attitudes, norms, or behaviors at baseline and demographics related to these outcomes at baseline. We will explore a variety of model specifications during our analyses and conduct diverse robustness checks given the quasi-experimental design. As we will know whether network nominations are reciprocal (ie, if ego A nominated first tier alter A, did first tier alter A nominate ego A in return?), we can evaluate the possibility of omitted variables or confounding events explaining the associations by examining how the type or direction of the social relationship between ego and alter affects the association between ego and alter (using a “network directionality” test) [57]. Additionally, we will also conduct a sensitivity analysis in which we estimate the bias in the association between ego and alter that might be caused by an omitted variable that is correlated with the prevalence of the outcome variable in both ego and alter [58]. This class of omitted variables includes those that explain friendship formation based on a trait (homophily) and confounding environmental factors that may affect the ego and alter relationships.

Network effects likely will not be uniform across subgroups. For this reason, we will conduct a series of subgroup analyses, looking at potential moderators of potential network effects based on what we learn about the SN characteristics from baseline data. By running a series of interaction models on our main effect analyses, we will consider whether diffusion differs depending on gender, LGBTQ+ identity, the strength of the connection, and other potential moderators such as age, ethnicity, experiences of violence, and program exposure.

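### For the binary SV/DV outcomes, the direction part of the network directionality test gives the same odds ratio both ways under the one model described, so it cannot separate influence from confounding

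*Protocol article*

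**What the plan says.** The social diffusion part of Analysis of SN Data sets out the model and the test in sequence.

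- **Unit:** "we will use the dyadic dataset of nominator-nominee pairs".
- **Model:** the effect of the contacts' "attitudes, norms, or behaviors at 24-month follow-up, controlling for both of their own attitudes, norms, or behaviors at baseline". The contact's baseline value is already a covariate, so the natural reading is that the exposure is the contact's 24-month value and the outcome is the focal youth's 24-month value.
- **Premise of the test:** "As we will know whether network nominations are reciprocal".
- **Purpose:** "we can evaluate the possibility of omitted variables or confounding events explaining the associations".
- **Contrast:** "examining how the type or direction of the social relationship between ego and alter affects the association between ego and alter".

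The same section states "The primary outcomes, SV and DV, were analyzed as binary variables", while most secondary outcomes are mean scale scores. It leaves the model specification open and plans a separate sensitivity analysis for an omitted variable, naming homophily and shared environment. Under Youth Recruitment, alter 2s differ from alter 1s in that "they were not asked to nominate peers or provide peer contact information". The Intervention Sites section places the start of each site's new program cycle after baseline data collection.

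**The concern.** A direction contrast helps against confounding only if influence and confounding predict different results. Influence running from nominee to nominator should appear in one direction and not the other; a shared cause should appear in both. That requires a coefficient that can differ by direction. When both peers' values come from the same wave and both baselines are adjusted for, the quantity estimated is a conditional association between two follow-up values, and for binary outcomes its odds ratio has no direction.

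At stake is the interpretation of the diffusion analysis, which is part of aim 2 and a stated hypothesis. Equal odds ratios for SV or DV would carry no information either way, and unequal slopes for a norms scale could reflect nothing more than unequal spread.

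**Working it through.** The article gives no sample size, power or significance level for this test, so there is no stated figure to reproduce. Let A be the nominator and B the nominee in a one-way tie; 0 is baseline and 1 is 24 months.

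**1. Binary outcomes, algebra.** Fix the baseline pattern (A0, B0) and write p_jk = P(A1=j, B1=k).

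- A1 on B1: OR = (p11/p01)/(p10/p00) = p11·p00/(p01·p10).
- B1 on A1: OR = (p11/p10)/(p01/p00) = p11·p00/(p10·p01).

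These are the same number. The fitted coefficients agree exactly if the product A0·B0 is also in the model, and almost exactly without it.

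**2. Binary outcomes, simulation.** 400,000 one-way dyads per scenario. Baseline prevalence is 27%, the control SV rate in the power section. Effects are assumptions: follow-up logit = −1.5 + 1.2 × own baseline, plus the terms shown. Entries are log-ORs.

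| Truth | A1 on B1 | B1 on A1 | A1 on B0 | B1 on A0 |
|---|---|---|---|---|
| B1 influences A1 (0.8) | 0.801 | 0.801 | 0.206 | 0.000 |
| B0 influences A1 (0.8) | 0.007 | 0.007 | 0.802 | −0.013 |
| Shared shock only (SD 1.0) | 0.740 | 0.740 | −0.001 | 0.018 |
| Shock (SD 0.9) and B0 influence (0.5) | 0.627 | 0.627 | 0.431 | −0.003 |

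The first two result columns are the described model. Dropping A0·B0 opened a gap between directions of at most 0.0003. The last two columns use the peer's baseline value, adjusted for the focal youth's own baseline, and these do differ by direction.

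**3. Scale outcomes.** Let σA² and σB² be the variances of A1 and B1 given both baselines, and σAB their covariance. The slopes are σAB/σB² (A1 on B1) and σAB/σA² (B1 on A1), so their ratio is σA²/σB².

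- True one-way influence 0.30, unit error variances: σB² = 1, σA² = 1 + 0.30² = 1.09. Slopes 0.30/1 = 0.300 and 0.30/1.09 = 0.275 (simulated 0.301 and 0.276).
- No influence, shared shock SD 0.6, own error SDs 1.3 and 0.8: σAB = 0.36, σA² = 1.69 + 0.36 = 2.05, σB² = 0.64 + 0.36 = 1.00. Slopes 0.36/1.00 = 0.360 and 0.36/2.05 = 0.176 (simulated 0.364 and 0.178).

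The case with no influence shows the larger directional gap.

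**4. Mutual versus one-way ties.** Here symmetry does not force equality.

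- Equal confounding (shock SD 0.7), influence 0.5 acting over four steps: log-OR 0.91 mutual, 0.73 one-way, 0.59 with no influence. The contrast responds to influence.
- No influence, stronger shared shock in mutual ties (SD 1.3 versus 0.7): 1.05 mutual, 0.42 one-way. The ordering is the same.

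**5. Realistic size.** The number of dyads is not given. Assuming 700 baseline one-way dyads and both members followed, 700 × (746/953)² = 700 × 0.613 ≈ 430. With 600 runs per cell and true influence ORs of 2, 3 and 5 from nominee to nominator only:

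- Described model: median ORs 1.80 vs 1.80, 2.55 vs 2.55 and 3.96 vs 3.96; directional difference significant in 0% of runs (0 to 0.2% if influence is lagged by 12 months).
- Peer's baseline value as exposure: 1.69 vs 1.00, 2.19 vs 0.98 and 3.07 vs 1.00; directional power 33%, 68% and 93%, falling to 18%, 39% and 69% if influence acts only within the follow-up year.

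**The case against.** The strongest reply is that the article leads with reciprocity and refers to type or direction of the tie. It never says that the two directions will be compared within the same one-way dyads. The mutual versus one-way contrast does respond to influence when confounding is equal across tie types (step 4). A reader might infer that the whole directionality test is empty, or that the plan would take a null result as proof of confounding. The documents support neither: symmetry disables only the direction contrast, and no such decision rule is printed. Nor is it true that scale slopes must be equal; step 3 shows that they can differ.

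Two further replies concern coverage. The specification is left open, and a separate omitted-variable analysis addresses homophily and environment. Both are true, so the confounding question does not rest on this test alone. Neither makes the direction contrast valid under the one model described, and the article states affirmatively that the test can evaluate confounding.

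A last reply concerns the remedy. Baseline values precede the new program cycle, so a model with the peer's baseline value as exposure tests peer influence in general, not the spread of a change that the program produced. That stands and limits what the added model may be said to show.

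The reciprocity contrast has its own weakness. It needs confounding to be equal across tie types, which is doubtful when the same section names homophily as a source of bias. Reciprocity is also unobserved for alter 1–alter 2 ties, because alter 2s made no nominations.

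**Conclusion.** The concern holds in a limited form. If the exposure is the contact's 24-month value, the direction contrast for binary SV/DV outcomes is null under influence and under confounding alike. This is an algebraic identity, accurate to within fitting error, and does not depend on the simulated effects. For scale outcomes the directional gap is a residual-variance ratio and is not reliable evidence. The mutual versus one-way contrast remains usable only under an unstated and doubtful assumption of equal confounding.

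The dyad count, effect sizes and power figures are assumptions; they show the pattern and are not estimates for this study. The point affects one robustness check on the diffusion analysis. It does not show that diffusion cannot be studied, and it leaves the primary difference-in-differences estimate untouched.

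**What to change.** In the social diffusion part of Analysis of SN Data:

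1. Keep the model of both peers' 24-month values for the association, but do not use its direction contrast as evidence for or against confounding.
2. Add a direction contrast with the peer's baseline value as exposure for the focal youth's 24-month outcome, adjusted for the focal youth's own baseline. Fit both directions on the same one-way dyads and test the difference with dyad-clustered standard errors.
3. Limit it to ties in which both members were asked to nominate, which excludes alter 1–alter 2 ties.
4. Report it as a check on peer influence in general, because baseline values precede the program cycle.
5. State that the mutual versus one-way contrast assumes equal confounding across tie types, and rely on the planned omitted-variable sensitivity analysis for the confounding question.

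The cost is revised wording and one added model on data already collected. The drawback is modest power for small effects. The signal can also fade over 24 months: in the four-step one-way scenario of step 4 the baseline-exposure log-ORs were only 0.042 and 0.004. A null result from the added contrast should therefore not be read as absence of influence.
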